### Sample size

According to the statistical requirements of neuroimaging studies, 12–15 individuals in each group is the reasonable sample size for stable cerebral responses [22, 23]. Considering a drop-out rate of 20% and possible excessive head motion during scanning, a sample size of 24 in each group is required, and a total of 72 PDM patients will be recruited.

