### Clinical data analysis

The Kolmogorov-Smirnov test will be used to test the normal distribution of continuous variables. Continuous variables on normal distribution will be presented by mean ± standard deviation, while continuous variables of skewed distribution were expressed as medians and interquartile ranges (IQRs). Analyses will be performed on an intention-to-treat basis. Multiple imputations will be used to handle the missing data. Paired samples *t*-test will be used to compare the clinical outcomes between baseline and end of treatment in each group. Since there are three groups (acupuncture group, moxibustion group, and waiting-list group) with two time points (pre-treatment and post-treatment), the repeated measures analysis of variance (ANOVA) will be employed to analyze the clinical data. In the 2 × 3 group factorial design, the dependent variables were the clinical data collected from pre-treatment and post-treatment, and data in the three different groups will serve as the independent variable. ANOVA and chi-square test will be used to compare group differences at baseline. ANOVA with Šidák corrections will be used to compare the differences between the groups. Clinical data on skewed distribution will be compared using a non-parametric test. A two-sided test is applied for available data, and a *P* value of less than 0.05 is considered statistically significant. Missing data will be replaced by the data from the latest assessment.

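### Two conflicting rules for the same missing clinical data: multiple imputation, and carrying the latest assessment forward

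*Protocol article*

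**What the plan says.** One paragraph of the protocol article, under Clinical data analysis, contains four statements that bear on missing values:

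- the analysis population: "Analyses will be performed on an intention-to-treat basis";
- a first rule: "Multiple imputations will be used to handle the missing data";
- a sentence on sidedness and significance level that also mentions available data: "A two-sided test is applied for available data, and a *P* value of less than 0.05 is considered statistically significant";
- a second rule, which closes the paragraph: "Missing data will be replaced by the data from the latest assessment".

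Neither rule is called primary or sensitivity. Neither is tied to an outcome, a visit or a reason for missingness.

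The Sample size section sets the expected loss: "Considering a drop-out rate of 20% and possible excessive head motion during scanning, a sample size of 24 in each group is required". Under Measurements, VAS, CMSS and PCS are scheduled at baseline and at each treatment cycle, while SAS, SDS and SF-36 are scheduled at baseline and end of treatment only. The clinical comparison is a repeated measures ANOVA with three groups and two time points, before and after treatment.

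**The concern.** An intention-to-treat analysis of a before-and-after contrast needs an end value for every randomised patient, so the rule for missing end values is part of the estimate. Multiple imputation draws several plausible values from a model and pools the results. Carrying forward inserts one earlier value and treats it as observed. A given missing value cannot be handled both ways in one analysis, and two statisticians following this paragraph could report different results from the same data.

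The two rules also carry different risks. Carrying forward assumes that a patient who leaves would have stayed where she was last seen. In a three-cycle treatment course that assumption sets part of the later improvement to nil, and by different amounts in arms that improve at different rates or lose different numbers of patients. Patients cannot be blinded and one arm is an untreated waiting list, so unequal drop-out is plausible.

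**Working it through.** **1. Can the two rules be reconciled from the text?** Both stand under Clinical data analysis and both speak of missing data in general. The section on neuroimaging data gives no missing-data rule, so one cannot be read as clinical and the other as imaging. No other section ranks them. The conflict is in the text itself.

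**2. How many values are affected?** Inputs from the protocol: 72 patients, 24 per group, 20% drop-out.
- 0.20 × 72 = 14.4, about 14 end-of-treatment values.
- 0.20 × 24 = 4.8, about 5 per group.

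The group size of 24 does not follow from drop-out alone: 15 / 0.80 = 18.75, so 19. The rest is an allowance for head motion, for which no rate is given. Nothing below depends on it.

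**3. SAS, SDS and SF-36.** The latest assessment before a missing end value is the baseline, so the imputed change is baseline minus baseline = 0. This follows from the schedule alone. If drop-outs would otherwise have changed as completers did, an arm with true mean change f and drop-out d shows (1 − d) × f. At 20% in both arms the group difference becomes 0.80 of its true value.

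**4. VAS (likewise CMSS and PCS).** The article gives no trajectories, so these are assumptions. Mean change at cycles 1, 2 and 3:
- active: -1.5, -2.5, -3.0 cm;
- waiting list: -0.3, -0.5, -0.5 cm.

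Drop-out is spread evenly over the cycles and unrelated to outcome. The true difference at the end is -3.0 − (-0.5) = -2.50 cm.

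The mean value carried forward, for patients last seen at baseline, cycle 1 or cycle 2, is:
- active: (0 − 1.5 − 2.5) / 3 = -1.333;
- waiting list: (0 − 0.3 − 0.5) / 3 = -0.267.

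Expected mean per arm = (1 − d) × final change + d × mean carried forward.

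| Drop-out, active / waiting list | Active | Waiting list | Difference | Shrinkage |
|---|---|---|---|---|
| 20% / 20% | 0.8(-3.0) + 0.2(-1.333) = -2.667 | 0.8(-0.5) + 0.2(-0.267) = -0.453 | -2.21 | 0.29 / 2.50 = 11% |
| 30% / 10% | 0.7(-3.0) + 0.3(-1.333) = -2.500 | 0.9(-0.5) + 0.1(-0.267) = -0.477 | -2.02 | 0.48 / 2.50 = 19% |

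The bias in the contrast is d × (mean carried forward − final change) in one arm minus the same term in the other. With equal trajectories and equal drop-out the terms cancel and the bias is zero. In the first row drop-out is equal, so the whole 11% comes from the different course of improvement.

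**5. Simulation check.** 800 runs per scenario, two arms of 24, four visits. Assumed: baseline VAS 6, SD 1.8, correlation 0.6, linear improvement, and drop-out depending on the last observed value. Monte Carlo standard error of the estimates is about 0.02.

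| True difference; nominal drop-out by arm | Available cases | Multiple imputation | Carried forward |
|---|---|---|---|
| -2 (active improves by 2, control by 0); 20% / 20% | -2.00 | -2.00 | -1.68 |
| -2; 30% active / 10% control | -1.99 | -2.02 | -1.47 |
| -2; 10% active / 30% control | -2.03 | -2.00 | -1.92 |
| 0 (both improve by 2); 10% / 30% | -0.06 | -0.03 | -0.41 |
| 0 (both improve by 2); 20% / 20% | 0.00 | -0.01 | -0.01 |

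False-positive rates, in the same column order, are 4.5%, 2.6% and 14.1% in the fourth row, and 5.8%, 4.5% and 5.4% in the fifth. The fourth row resembles the trial's first aim, acupuncture against moxibustion: two equally effective treatments with unequal drop-out look different if values are carried forward.

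**The case against.** Several stronger readings are tempting, and the document does not support them.

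- **Three incompatible rules.** A reader might count "A two-sided test is applied for available data" as a complete-case rule. It stands in a sentence on sidedness and the significance level and may mean only the data being tested. It is ambiguous and adds to the confusion, but the firm conflict is between two rules.
- **Carrying forward is always biased, or always conservative.** Neither holds. With matching trend and drop-out the bias was about zero and the false-positive rate 5.4%. With equal improvement and unequal drop-out it created a difference of -0.41 where there was none.
- **Standard errors are shown to be too small.** Carrying forward ignores imputation uncertainty in principle, but no figure here shows the effect. The 14.1% false-positive rate goes with a biased estimate, so it is not evidence on the standard error.
- **The method will be chosen after the data are seen.** The article says that a detailed SAP was developed before the statistical analysis began, that the statisticians are independent of the research team, and that they are blinded to allocation. The SAP is not shown and may name one rule.

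It is also fair to say that every VAS figure rests on assumed trajectories, and that if acupuncture and moxibustion share a similar course and similar drop-out, their contrast is hardly touched. These points limit the size of the problem. They leave the conflict standing: if the SAP names a single rule, one of the two published sentences is wrong.

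**Conclusion.** The paragraph is wrong as written. It prescribes two different treatments of the same missing clinical values without qualification, and an intention-to-treat analysis of the clinical outcomes cannot be uniquely reproduced from it.

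Two parts of this need no assumed effect sizes or trajectories: the conflict itself, and the zero change assigned to every drop-out on SAS, SDS and SF-36 under carrying forward. The count of about 14 of 72 rests on the plan's own 20%.

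The size of the effect on VAS is illustrative: 11% to 19% shrinkage of a 2.50 cm difference under the stated trajectories. The simulations, under their own assumptions, ranged from almost no distortion to a false-positive rate of 14.1%. The bias requires arms that differ in improvement over time or in drop-out. Multiple imputation stayed close to the true difference in all five scenarios, in which drop-out depended only on observed values.

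**What to change.** In Clinical data analysis:

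1. Delete "Missing data will be replaced by the data from the latest assessment".
2. Keep multiple imputation as the single primary rule. State that the imputation model contains treatment group, the baseline value and, for VAS, CMSS and PCS, the values observed at the treatment cycles. SAS, SDS and SF-36 have no cycle values of their own to use.
3. Reword the sentence on two-sided tests so that it covers only sidedness and significance level and no longer refers to available data.
4. Label any other handling of missing values a sensitivity analysis.

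Align the SAP with this if it says otherwise. Separate imputation models per arm, a mixed model over all cycles or a delta-adjusted analysis are not needed to remove the conflict. A mixed model would also replace the planned two-time-point ANOVA, which is more than a change of wording.

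The cost is slightly more analysis work, for imputing and pooling results that the plan already promises. No new data are needed.

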### Neuroimaging data processing and analysis

The fMRI data will be preprocessed and post hoc analyzed by the SPM12 software (http://www.fil.ion.ucl.ac.uk/spm/) and CONN toolbox (http://www.nitrc.org/projects/conn) performed on MATLAB 2015b (MathWorks, Inc., Natick, MA, USA). The preprocessing steps will include slice timing correction, head motion correction, spatial normalization, spatial smoothing, and detrending. After data preprocessing, amplitude of low-frequency fluctuation, regional homogeneity, and functional connectivity will be used to investigate the cerebral responses of the different study groups. ANOVA will be used to evaluate possible cerebral responses in each group by within-group analysis (post-treatment minus pre-treatment). A threshold of voxel-wise *P* < 0.005 uncorrected and cluster-level *P* < 0.05 false discovery rate (FDR) corrected will be applied to all analyses. Pearson’s correlation test will be conducted to investigate the changes between fMRI data and corresponding clinical data in each group.

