**Methods:**

In this randomized controlled neuroimaging trial, 72 patients with PDM will be randomly assigned to three groups: acupuncture treatment group, moxibustion treatment group, and waiting list group. The acupuncture treatment group and moxibustion treatment group will receive acupuncture or moxibustion, respectively, for a total of 3 sessions over 3 consecutive menstrual cycles, and the waiting list group will not take acupuncture or moxibustion during these 3 menstrual cycles. The COX Menstrual Symptom Scale (CMSS), visual analog scale (VAS), and Pain Catastrophizing Scale (PCS) will be used to evaluate the clinical efficacy. The Self-rating Depression Scale (SDS), Self-rating Anxiety Scale (SAS), and 36-Item Short Form Health Survey (SF-36) will be used to assess the mental state and quality of life at baseline and at the end of treatment. Functional magnetic resonance imaging (fMRI) will be performed for detecting the cerebral activity changes at baseline and at the end of the treatment. The clinical data and imaging data will be analyzed among the groups. Correlation analysis will be conducted to investigate the relationship between brain functional changes and symptom improvement.

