**Discussion:**

The application of the randomized controlled neuroimaging trial will provide objective and valid evidence about how acupuncture and moxibustion treatment relieve menstrual pain. The results of this study would be useful to confirm the potential similarities and differences between acupuncture and moxibustion in clinical efficacy and central mechanism for patients with PDM.

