### Methodological quality control is crucial to ensure the repeatability of the results

Strict quality control is essential to improve the reliability of the study and should be used throughout the test. In this trial, quality control will be strengthened in three aspects. Firstly, when recruiting patients, we establish rigorous inclusion and exclusion criteria. In addition to demographic characteristics, other factors such as the usage of medication that may influence cerebral activities are also considered. Because PDM is often accompanied with anxiety and depression, SAS and SDS are used to assess the emotional state. Secondly, in order to ensure the curative effect, unified training will be conducted before the acupuncture and moxibustion operation. After the training is qualified, the two acupuncturists will follow the strict and standard operating procedures. Thirdly, baseline data will be collected on the first day of the menstrual cycle. Participants will be asked to maintain their regular lifestyle and avoid staying up late and ingesting alcohol and caffeine 24 h before the scan. Meanwhile, participants will be asked to follow uniform instructions, wear earplugs, close their eyes, and remain relaxed and awake during the scan.

Acupuncture and moxibustion are effective interventions in PDM treatment, but their central mechanism remains unclear. This trial is designed to investigate the differences between acupuncture and moxibustion in clinical efficacy and central mechanism through the following two aspects. On the one hand, the symptom improvement and cerebral responses to acupuncture, moxibustion, and waiting list will be compared, and on the other hand, the correlation between the cerebral activity changes and clinical variables’ improvement will also be analyzed.

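### The imaging section specifies only within-group tests and defines no between-group test, although the article announces a comparison of cerebral responses across the three arms

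*Protocol article*

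**What the plan says.** Under the heading on neuroimaging data processing and analysis, the protocol article names three measures: amplitude of low-frequency fluctuation (ALFF), regional homogeneity (ReHo) and functional connectivity (FC). These "will be used to investigate the cerebral responses of the different study groups". Two inferential procedures follow. The first is the test of change: "ANOVA will be used to evaluate possible cerebral responses in each group by within-group analysis (post-treatment minus pre-treatment"). The second concerns association with symptoms: a Pearson "correlation test will be conducted to investigate the changes between fMRI data and corresponding clinical data in each group". The significance rule is "A threshold of voxel-wise *P* < 0.005 uncorrected", combined with a cluster-level P < 0.05 that is "false discovery rate (FDR) corrected will be applied to all analyses".

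Elsewhere the article describes a comparison between arms. The abstract's methods paragraph says: "The clinical data and imaging data will be analyzed among the groups". The abstract's discussion expects the results to "confirm the potential similarities and differences between acupuncture and moxibustion in clinical efficacy and central mechanism". In the main Discussion, under the heading on methodological quality control, the article says that "the symptom improvement and cerebral responses to acupuncture, moxibustion, and waiting list will be compared". None of these places names a test.

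The clinical data analysis section does name between-group tests: a repeated measures ANOVA over three groups and two time points, and an ANOVA with Šidák correction for differences between groups. Both are stated for clinical data.

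**The concern.** The announced question is between arms, while the stated imaging tests are within arms. Followed literally, the plan yields three maps of change and three sets of correlations. A reader who wants to know whether acupuncture and moxibustion act differently on the brain could then only set the maps side by side and note which regions appear in one and not in another. That is not a test of a difference: a region can pass in one arm and fail in another when the true changes are identical.

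A within-arm change also mixes any treatment effect with whatever else alters between two scans about three months apart, such as time and repeat scanning. The randomised waiting-list arm can separate these, but only if change in the treated arms is tested against change in that arm. At stake is the trial's conclusion on mechanism.

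**Working it through.** **1. The passages side by side.**

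| Place in the protocol article | What it announces or specifies | Test between arms named? |
|---|---|---|
| Abstract, Methods | Imaging data analysed among the groups | No |
| Abstract, Discussion | Similarities and differences in central mechanism | No |
| Methodological quality control | Cerebral responses of the three arms compared | No |
| Clinical data analysis | Repeated measures ANOVA; Šidák-corrected ANOVA between groups | Yes, for clinical data |
| Neuroimaging analysis | ANOVA labelled within-group, in each group; Pearson in each group | No |

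The only section that assigns tests to the imaging data assigns none to the comparison announced elsewhere.

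**2. How often within-arm maps would disagree when the arms do not differ.**

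The plan has no figure of its own here to reproduce, and it gives no imaging effect size, SD or power. The inputs are:

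- Threshold: voxel-wise 0.005, from the neuroimaging section. Two-sided is an assumption, because sidedness is not stated for imaging.
- Scans per arm: 24 randomised and 20% drop-out, from the sample size section, so 24 × 0.80 = 19.2, taken as 19. This assumes no further loss to head motion. All 24 is shown as the other case.
- True standardised change d (mean change divided by the SD of change), equal in two arms: assumed 0.3, 0.5, 0.6 and 0.8.
- Single voxel, with the cluster-level step ignored.

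The chance p that one arm passes is the power of a one-sample t test on change, with n − 1 degrees of freedom and noncentrality d√n. For n = 19 the critical t is 3.197. At d = 0.5 the noncentrality is 0.5 × √19 = 2.179 and p = 0.195. The chance that exactly one of two independent arms passes is 2p(1 − p) = 2 × 0.195 × 0.805 = 0.314.

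| d in both arms | p, n = 19 | Exactly one passes, n = 19 | p, n = 24 | Exactly one passes, n = 24 |
|---|---|---|---|---|
| 0.3 | 0.051 | 0.10 | 0.072 | 0.13 |
| 0.5 | 0.195 | 0.31 | 0.286 | 0.41 |
| 0.6 | 0.318 | 0.43 | 0.453 | 0.50 |
| 0.8 | 0.617 | 0.47 | 0.780 | 0.34 |

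Because the true changes are equal, every such disagreement is spurious. A two-sample test on change at the same threshold would be falsely positive with probability 0.005. The expression 2p(1 − p) cannot exceed 0.50, and it falls again once the effect is large enough for both arms usually to pass: at d = 1.0 with n = 19, p = 0.857 and the chance is 0.25.

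**3. What a direct test can detect.**

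The two-sample test on change has 2n − 2 degrees of freedom and noncentrality d√(n/2). Under the same assumptions, the standardised effects detectable with 80% power are:

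| Scans per arm | Change within one arm | Difference in change between two arms |
|---|---|---|
| 19 | 0.94 | 1.25 |
| 24 | 0.82 | 1.10 |

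**The case against.** The strongest reply is that a between-arm test may well be intended. The abstract and the discussion both announce the comparison, and the article refers to a detailed SAP that covers neuroimaging and is not shown. The ANOVA sentence can also be read charitably. Post minus pre leaves one value per patient, so within a single arm there is no factor for an ANOVA to test; it makes sense only if group is the factor. The sentence may be a garbled three-arm ANOVA of change. This stands as far as it goes: a reader might infer that brain responses will never be compared between arms, and the documents do not support that. It does not rescue the section, which states a method, labels it within-group and places it in each group. If a three-arm test was meant, the sentence still has to be corrected.

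Two further inferences fail. The article does not say that the waiting list will be set aside, since it is listed in the announced comparison. Nor are the maps without error control, because the cluster-level FDR rule applies to all imaging analyses; only an informal comparison between maps would lack it.

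It is also tempting to quote about 50% disagreement, which is what P < 0.05 with 19 scans gives at 0.5 SD. That is not the plan's voxel threshold; at 0.005 the figure is 31%.

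On the correlations, the third aim in the Background is to explore associations under acupuncture or moxibustion. Per-arm Pearson tests serve that aim, and no comparison of correlations between arms is promised. Replacing them would be a preference and is not part of this point.

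**Conclusion.** The point holds as a contradiction within the article. The imaging section specifies within-group tests and defines no between-group test, while the abstract and discussion announce a comparison across the arms. It cannot be put down to detail left to the SAP, because the published sentence fixes a method that does not answer the announced question. It should be corrected before the imaging data are analysed.

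The size is illustrative: a spurious difference between two equal arms at a voxel in about 10% to 47% of cases for assumed changes of 0.3 to 0.8 SD with 19 scans per arm, against 0.5% for a direct contrast. This rests on the assumed effect sizes, equal true change, a two-sided threshold, no head-motion loss and a single voxel. With the cluster step included the figures would differ. The logical point, that separate maps do not test a difference, needs none of these assumptions.

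**What to change.** Reword the imaging section so that the main analysis is the group effect on post-minus-pre values (equivalently, the group-by-time interaction) across the three arms for ALFF, ReHo and FC. Follow it with the three pairwise contrasts, corrected for their number, under the cluster threshold already stated. Keep the within-group maps as description and say that they will not be used to claim differences between arms. The per-arm Pearson correlations may stay if labelled exploratory; any claim that a correlation differs between arms needs a direct test, such as a group-by-brain-change interaction. If the SAP already contains such a model, align the published wording with it.

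The cost is wording and a different second-level model, with no new data or scans. The real downside is sensitivity: the between-arm contrast needs a standardised effect of about 1.25 for 80% power at 19 per arm, against 0.94 for a within-arm change, so fewer regions are likely to be declared. That limitation should be stated.

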#### Measurements for the quality of life

The 36-item Short Form Health Survey (SF-36) will be used to evaluate the quality of life [32]. The scale contains 8 dimensions including physical functioning, role limitations due to physical health problems, role limitations due to emotional problems, social functioning, bodily pain, vitality, mental health, and general health.

The VAS, CMSS, and PCS will be measured at baseline and every menstrual cycle throughout the treatment. The SAS, SDS, and SF-36 will be measured at baseline and at the end of the treatment.

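### The imaging 5% level holds at best within one map: over the nine or more maps planned the chance of a false cluster is about 22–37%, and no correction is stated for the per-group correlations

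*Protocol article*

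**What the plan says.** All of the imaging error control stands in the protocol article under Neuroimaging data processing and analysis.

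- Metrics: "amplitude of low-frequency fluctuation, regional homogeneity, and functional connectivity will be used to investigate the cerebral responses of the different study groups".
- Contrasts: "ANOVA will be used to evaluate possible cerebral responses in each group by within-group analysis (post-treatment minus pre-treatment"), that is, one change map per group and metric. The Discussion, under the heading on methodological quality control, adds a comparison between groups: "the symptom improvement and cerebral responses to acupuncture, moxibustion, and waiting list will be compared".
- Threshold: clusters are formed at voxel-wise P<0.005 without correction, and a cluster-level P<0.05, "false discovery rate (FDR) corrected will be applied to all analyses".
- Correlations: "Pearson’s correlation test will be conducted to investigate the changes between fMRI data and corresponding clinical data in each group".

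The scales available for correlation are listed at the end of the Symptoms measurement section. "The VAS, CMSS, and PCS will be measured at baseline and every menstrual cycle throughout the treatment", and SAS, SDS and SF-36 are taken before and after treatment, which makes six. The text does not say which of them count as corresponding data.

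Under Clinical data analysis, a Šidák correction is given for the group comparisons of clinical outcomes. No counterpart appears for imaging metrics, contrasts or correlations.

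**The concern.** Cluster-level FDR is computed over the clusters of one map. It does not adjust for how many maps are read. The article commits to this rule for every imaging analysis and names neither a primary metric nor a primary contrast. A reader will take the corrected 5% to describe the imaging results as a whole, and it does not.

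The cluster-forming threshold raises a second, smaller issue. Parametric cluster P values rest on an approximation that is best at high thresholds. At a lenient threshold such as 0.005, long-range spatial correlation in the noise can produce large clusters more often than the approximation allows.

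Third, a cluster rule does not govern correlations of values extracted from regions, and no other threshold or correction is given for them.

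At stake are aims 2 and 3 in the Background: the central mechanism, and the link between brain change and symptom change. The article says the results would help to confirm similarities and differences between the two treatments, and that they will be objective and valid evidence of mechanism. That language needs an error rate that holds over the set of analyses reported.

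**Working it through.** The article states no error rate over the set of imaging analyses, so there is no figure of its own to reproduce.

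**Inputs from the article.** Three metrics; three groups; cluster-level 0.05 per map; six clinical scales. Three metrics is a minimum, because the number of connectivity seeds or networks is not stated.

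**1. Maps.** With no true effect anywhere, every declared cluster is false, so FDR at 0.05 means at most a 5% chance of any false cluster in a map. With m independent maps, each exactly at 5%, the chance of at least one is 1 − 0.95^m.

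- 3 metrics × 3 groups = 9 maps: 1 − 0.95^9 = 0.370.
- 12 maps (adding one overall between-group map per metric): 0.460.
- 18 maps (adding three pairwise contrasts per metric instead): 0.603, an overstatement, because pairwise contrasts share data with the within-group maps.

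The three metrics come from the same BOLD series, so independence is an upper case. Treating them as equally correlated within a group, with groups independent, gives for nine maps:

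| Correlation between metrics | Chance of at least one false cluster |
|---|---|
| 0 | 37% |
| 0.3 | 34% |
| 0.5 | 32% |
| 0.7 | 28% |
| 0.9 | 22% |

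**2. Cluster-forming threshold.** The article gives neither the smoothing kernel nor the cluster inference method. The check therefore assumes random-field cluster P values with FDR over clusters, 19 per group (24 × 0.8 = 19.2) and several noise structures. Share of null maps with a false cluster, one direction:

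| Null simulation | Gaussian, 0.005 v 0.001 | Long-tailed, 0.005 v 0.001 |
|---|---|---|
| Two-sample maps, 200 runs (Gaussian) and 800 runs (long-tailed) | 2.5% v 1.5% | 7.5% v 4.4% |
| Within-group maps, 120–200 runs per setting | 0% v 0–1.5% | 3.3–4.5% v 0–2% |
| Within-group maps, another simulation | about 5% v about 5% | about 22% v about 14% |

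Under long tails, 0.005 is worse than 0.001 in every simulation. The size ranges from below 5% to about 22%, and in the last row 0.001 does not restore 5% either. Under Gaussian smoothness neither threshold shows an excess.

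**3. Correlations.** Assume one extracted region per metric and group, each test at 0.05. The expected number of false positives under the null is 0.05 × (3 groups × 3 metrics × scales).

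- Two scales: 18 tests, 0.05 × 18 = 0.9 expected. The chance of at least one is 60% if independent, and about 45% if metrics and scales each correlate at 0.7.
- Six scales: 54 tests, 0.05 × 54 = 2.7 expected. The chance is 94% if independent, and about 71–72% at correlation 0.7.

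At 15 analysable patients per group, |r| must exceed about 0.51 to reach P<0.05 (0.46 at 19, 0.40 at 24). Any false link would therefore also look strong.

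**The case against.** The best defence is that the article refers to a detailed SAP covering the neuroimaging analysis, which is not shown. The correlation threshold, the choice of regions and scales, and any correction across maps may be settled there. This stands for the correlations. That they are uncorrected, or number in the dozens, is something a reader might infer, but the article states neither. The restriction to corresponding clinical data may mean only two scales, and voxel-wise correlation maps could fall under the cluster rule. The correlation figures are therefore conditional. The defence carries less weight for the maps, because there the article does state its rule, for all analyses, with no further layer.

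A reader might also infer that false regional findings are likely. For the maps alone the documents do not support that: 22–37% over nine maps is well above 5% but below one half, and it assumes no true effect anywhere.

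Nor do they support saying that the 0.005 threshold by itself breaks the 5% level. Cluster-level FDR is a recognised form of correction, the excess depends on smoothness that the article does not give, and one set of long-tailed runs stayed under 5% per direction.

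Finally, aim 3 is worded as exploration and aim 2 concerns a potential mechanism. That lowers the weight of the point. It does not remove it, since the article elsewhere promises confirmation and valid evidence.

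**Conclusion.** The point holds. The 5% cluster-level rate applies at best within a single map. Over the nine within-group maps the chance of at least one false cluster is about 22–37%, assuming a complete null, exactly 5% per map, and metric correlations between 0.9 and 0. It is higher if between-group maps are counted too.

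The threshold of 0.005 is a secondary weakness. It is more error-prone than 0.001 if parametric inference is used on data with long-range smoothness, by an amount that cannot be fixed from the article.

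For the correlations, the article states no correction. If regional values are extracted and tested at 0.05, one region per metric, 0.9 to 2.7 false positives are expected under the null for 18 to 54 tests. The point deserves a change before the imaging data are analysed, but it does not undermine the trial.

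**What to change.** - Use permutation cluster inference, which does not rest on the smoothness approximation. Failing that, form clusters at P<0.001, accepting that this may not fully restore 5% under long-range smoothness.
- Name one imaging metric as primary, with the group-by-time contrast as its primary test, since the aim is to compare groups.
- Correct across whatever maps remain confirmatory, using their actual number. With nine, Bonferroni gives 0.05/9 = 0.0056 per map. Dividing by three for the metrics alone would leave 1 − (1 − 0.0167)^9, about 14%, over nine maps. Label all other maps exploratory.
- Limit correlations to one clinical scale named in advance and to regions from the primary contrast, with FDR over that family. The article ranks no clinical outcome as primary, so the scale has to be chosen explicitly.
- If the SAP already contains such rules, align the article's wording with them.

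The cost is wording and analysis settings; no data collection changes. The downside is that fewer clusters and correlations will reach significance.
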